### Sample size

The sample calculation considered two independent samples with an estimated proportion of the ulcer healing rate of 75% for group 1, which will be treated with cell therapy, and 30% for group 2, which will be treated with hydrogel dressing. Assuming a test power of 80% and a significance level of 5% for a two-sided test, the sample was defined as 20 participants for group 1 and 20 participants for group 2 (1:1 allocation). This study was designed to be analyzed with intention to treat (ITT).

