#### Efficacy.

Improvement in limb perfusion [34]: Assessed by thermography [35,36] (significant increase in limb temperature > 0.3 ºC), vascular ultrasound with Doppler (flow wave characteristics and flow velocity incrementation), ABI [29,30] (increase in ABI value ≥ 0.15 for participants with ABI < 0.9), transcutaneous capnography [37] (incrementation ≥ 10% in O_2_ levels and/or decrease ≤ 10% in CO_2_ levels measured at the base of the hallux and the ankle, behind the medial malleolus) and WIfI (the Society for Vascular Surgery Lower Extremity Threatened Limb Classification System: risk stratification based on wound, ischemia, and foot infection) [38,39].Improvement in quality of life: assessed by the SF-36 scale (Medical Outcomes Study 36 – Item Short-Form Health Survey) [40].Reduction in pain: Assessed by the Visual Analogue Scale (VAS) [41] and reduction in the use of analgesics (quantitatively and qualitatively).Partial ulcer healing: Assessed by measuring epithelialization of the ulcer. The total ulcer area will be analyzed using the area measurement tool in the free software ImageJ™ [42,43].Improvement in health perception: Assessed by the EQ-5D scale by EuroQol Group [44].Clinical improvement: Observed through physiological (blood pressure) and laboratory parameters (glycemia, glycated hemoglobin, HDL, LDL, total cholesterol, triglycerides, leukogram, hematocrit, uric acid, urea, creatinine, CRP, sodium, potassium, alkaline phosphatase (ALP), alanine transaminase (ALT), aspartate transferase (AST), gamma-glutamyl transferase (GGT), bilirubin, total protein, albumin, prothrombin time (PT), partial thromboplastin time (PTT)).Formation of granulation tissue in the ulcer.Changes in the systemic inflammatory profile with a predominantly cellular immune response through analysis of immunomodulatory cytokines (Th1, Th2, and Th17) [45,46].

### 
Participant timeline

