### Sample size and Statistics

The results obtained through the primary and secondary outcomes will be tabulated weekly in an electronic spreadsheet by the study monitoring team. A sample of 40 participants is estimated. The data will initially be evaluated using descriptive statistics, with median/variance and/or mean/standard deviation analyses for quantitative variables and contingency table analyses for categorical/qualitative variables. To effectively recruit the intended number of participants, our strategy involves having study team members to actively engage with patients in the outpatient clinics and wards of HC-FMB. This direct approach will ensure that we connect with a wide range of patients who meet the criteria to participate in the study, maximizing our chances of success.

All data monitored in the study for Group 1 (cell therapy) and Group 2 (control) will be statistically compared. Quantitative data will be evaluated for their distribution (using the Shapiro-Wilk normality test) and compared using the T-test or the Wilcoxon test, depending on the type of distribution of the variables. For categorical variables, differences will be evaluated using Pearson’s Chi-square test or Fisher’s exact test. Bonferroni coefficient and multivariate analysis will also be used. In all statistical tests, the significance level of the independent variable will be set at 5% (p < 0.05).

Finally, the evaluation of the entire data set using multiple correspondence analysis (MCA) is proposed. For its application, each quantitative variable will be categorized according to the distribution quartiles of their respective data.

Categorical variables will be evaluated by means of Fisher’s exact test, continuous variables will be compared with non-parametric methods such as the Mann-Whitney test or U test, pairwise comparisons will be evaluated with the Wilcoxon test, multivariate analyses will be evaluated with regression analysis Cox curves, long-term clinical analyzes will be compiled into Kaplan Meir curves.

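### The rule for categorical variables sends an ordered class such as WIfI to Pearson or Fisher, valid tests that ignore order; the rank test already named in the plan would suit it better

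*Protocol article*

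**What the plan says.** The section Sample size and Statistics recognises two kinds of variable, quantitative (or continuous) and categorical, and gives the tests for each kind twice.

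- Categorical, first statement: "For categorical variables, differences will be evaluated using Pearson"'s chi-square or Fisher's exact test.
- Categorical, second statement: "Categorical variables will be evaluated by means of Fisher"'s exact test, with no mention of Pearson.
- Quantitative, first statement: "compared using the T-test or the Wilcoxon test, depending on the type of distribution of the variables".
- Continuous, second statement: "exact test, continuous variables will be compared with non-parametric methods such as the Mann-Whitney test or U test".

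Neither statement has a rule for ordered categories.

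Under Secondary outcomes, Efficacy, the item "Improvement in limb perfusion" includes WIfI, described as "risk stratification based on wound, ischemia, and foot infection". Thermography, ABI and the transcutaneous measurements in the same item carry numerical thresholds for improvement; WIfI carries none. The section Sample size states that "the sample was defined as 20 participants for group 1 and 20 participants for group 2 (1:1 allocation").

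**The concern.** A risk stratification is ordered: one class is better or worse than the next. Under the stated two-way split it is categorical, so it goes to Pearson or Fisher. On a table with two arms and several classes, both tests give the same p-value if the classes are shuffled. They therefore spread their power over every kind of difference between the arms, including patterns with no clinical meaning, while the outcome is worded as improvement. With 40 participants, a secondary outcome has little power to spare. The plan already names a test that uses order, but restricts it to continuous variables.

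**Working it through.** **1. The plan's own figure.** Healing 75% v 30%, two-sided 5%, 80% power, pooled-variance formula:

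n = [1.960·√(2·0.525·0.475) + 0.842·√(0.75·0.25 + 0.30·0.70)]² / 0.45² = (1.384 + 0.531)² / 0.2025 = 18.1, so 19 per arm.

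The stated 20 per arm is reproduced to within one participant. Healing is binary, so the question of order does not arise for it.

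**2. What ignoring order means.** An illustrative table with 20 per arm and four classes from best to worst: Group 1 has 10, 5, 3, 2 and Group 2 has 5, 5, 5, 5.

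- Pearson (equal arms): Σ(a−b)²/(a+b) = 25/15 + 0/10 + 4/8 + 9/7 = 3.45 on 3 df, p = 0.33.
- Mann-Whitney with tie correction: the midranks are 8, 20.5, 29.5 and 37. The Group 1 rank sum is 80 + 102.5 + 88.5 + 74 = 345, against an expectation of 20·41/2 = 410. The variance is (20·20/12)·[41 − Σ(m³−m)/(40·39)] = 33.33·(41 − 5190/1560) = 1256. So z = −65/35.4 = −1.83, p = 0.07.

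Now put the same four columns in another order: Group 1 has 5, 2, 10, 3 and Group 2 has 5, 5, 5, 5. Pearson is still 3.45. The Group 1 rank sum becomes 27.5 + 28 + 250 + 109.5 = 415, so z = 5/35.4 = 0.14, p = 0.89. Only the rank test separates a consistent shift from a scrambled pattern.

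**3. Power with 20 per arm, two-sided 5%.** From the documents: 20 per arm and the 5% level. Assumed, because the documents do not give them: the number of classes, the control shares and a proportional-odds shift. Cumulative odds in Group 1 = OR × cumulative odds in Group 2. Pearson and Mann-Whitney were simulated with 40,000 trials per setting, and the exact Fisher-Freeman-Halton test with at least 5,000.

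Four classes, control shares 25/25/25/25, 10/20/30/40 or 5/10/25/60% (ranges run over the three sets of shares and, for the middle column, both tests):

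| Odds ratio | Pearson or Fisher | Mann-Whitney | Gap (points) |
|---|---|---|---|
| 1 (no effect) | 3–5% | 5% | – |
| 2 | 12–14% | 21–23% | 7–9 |
| 3 | 28–31% | 44–47% | 15–17 |
| 4 | 44–48% | 64–66% | 17–20 |
| 5 | 58–61% | 76–78% | 17–19 |
| 6 | 68–71% | 84–86% | 16 |
| 8 | 80–84% | 92–94% | 10–12 |
| 12 | 91–94% | 98–99% | 4–6 |

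Three equal classes: the gap is about 5–6 points at OR 2, 9–12 at OR 3, 10–13 at OR 5, 7–9 at OR 8 and 4–5 at OR 12, that is, about 4 to 13 points.

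No tested setting exceeds 5% under no effect by more than simulation error. In every setting with an effect, the test that ignores order has less power.

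**4. If WIfI is reduced to improved or not improved,** the table is 2×2. Two classes have no order to discard, and this loss does not arise.

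**The case against.** The strongest reply is that the article never says WIfI will be tested as a table of unordered classes. Most of its neighbours in the perfusion item have responder thresholds, so WIfI might be read as improved or not improved; or it might be scored and treated as quantitative. Either reading is possible, and neither would incur this loss. But the text gives WIfI no threshold and no score, and the rule it does state leads to Pearson or Fisher.

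A second reply is that the choice of test for one component of a secondary outcome belongs in the SAP. That would answer a complaint that detail is missing. Here the assignment is stated, twice, and an SAP that followed it would inherit it.

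Four stronger readings are tempting, and the documents do not support them:

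- A reader might infer a fixed loss of some 14 to 18 points. That size holds only for about four classes and mid-range odds ratios, and the documents supply neither.
- A reader might count the Doppler wave characteristics and analgesic use as ordered too. No ordered wave class is defined, and "reduction in the use of analgesics (quantitatively and qualitatively") may mean amount and type of drug, where type has no order.
- A reader might infer that the planned tests are invalid. They are not; both hold the 5% level.
- A reader might infer that a significant result could not be interpreted. The planned descriptive contingency tables would show the direction, although the p-value itself does not test it.

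**Conclusion.** The point holds as a matter of efficiency, confined to WIfI and any other outcome that is recorded as an ordered class. Under the stated rule such an outcome would be compared with a valid but less sensitive test. Assuming a proportional-odds shift with odds ratios from 2 to 12 and 20 per arm, the loss is about 4 to 20 points of power with four classes, largest at odds ratios 3 to 6, and about 4 to 13 points with three classes. It is nil if WIfI is analysed as improved or not improved. Total epithelialization and major amputation, the primary outcomes, are binary, so neither their analysis nor the sample size is affected. This is a worthwhile correction of wording for a secondary outcome, not a threat to the trial's main conclusion.

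**What to change.** Add to Sample size and Statistics, before any comparative data are seen, wording such as: *WIfI, and any other outcome recorded as an ordered class, will be compared between groups with the tie-corrected Wilcoxon-Mann-Whitney test and reported as the probability of a better class, or as a common odds ratio, with a 95% confidence interval. Pearson's chi-square and Fisher's exact test will be used only for binary and unordered variables.* If WIfI is meant to be analysed as improved or not improved, state that and define improvement instead.

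The cost is one or two sentences. No new data or participants are needed, and there is no added type I error if the choice is fixed in advance. The small downside is that a rank test has less power than Pearson or Fisher when the difference between the arms does not run in one direction.

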**Methods:**

An open randomized clinical trial will be carried out with two groups of twenty patients with CLI: In group 1, 2g of abdominal adipose tissue will be taken to produce ASCs. These cells will then be expanded in a lab (cell processing center) for 14–21 days before being applied to the lesion using bio-dressings and perilesional subcutaneous injections. Group 2 will receive conventional treatment with hydrogel-based dressing. There will be regular clinical assessments, supplementary tests, and photo documentation. The main efficacy outcome will be partial or complete healing of the wound. Safety outcomes will be monitored for infections, gangrene, amputations, and death. Participants will be monitored for 90 days. Cases of major amputation of the studied limb will not be included. The results will be evaluated by an independent external evaluator who is blind to the groups. Considering the high prevalence and socioeconomic consequences related to CLI and limb amputation, this study is expected to provide a positive social and financial impact on the Brazilian Unified Health System.

ClinicalTrials.gov: NCT06326203.

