### Primary outcomes

#### Safety.

Absence of major amputations (ankle, leg, or thigh).EfficacyTotal ulcer epithelialization and limb salvage rate (non-occurrence of a major amputation).

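### The trial is sized for one healing test at an unadjusted 5%, but two primary events are listed and Bonferroni covers an unnamed family, so the stated power and error rate are not secured together

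*Protocol article*

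**What the plan says.** Three sections of the protocol article bear on this point.

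- *Sample size* plans for one binary outcome. It takes an "estimated proportion of the ulcer healing rate of 75% for group 1" and "30% for group 2, which will be treated with hydrogel dressing". The design values are given as "Assuming a test power of 80% and a significance level of 5% for a two-sided test", and "the sample was defined as 20 participants for group 1 and 20 participants for group 2 (1:1 allocation"). No adjustment for multiple outcomes enters the calculation.
- *Primary outcomes* gives as primary safety outcome "Absence of major amputations (ankle, leg, or thigh"). As primary efficacy it gives total epithelialization of the ulcer together with the limb salvage rate, which it defines as no major amputation. That makes two distinct events, one of them listed twice.
- *Sample size and Statistics* says that all monitored data will be compared between the groups. It adds: "Bonferroni coefficient and multivariate analysis will also be used. In all statistical tests, the significance level of the independent variable will be set at 5" per cent. No family, number of tests or order of testing is given. For categorical outcomes the section first allows Pearson's chi-square or Fisher's exact test. Its last paragraph on testing names only Fisher's.

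**The concern.** The sample size is tied to one test at one threshold. The statistics section does not say that healing will be tested at that threshold, or that healing is the only outcome on which a primary claim can rest. Two courses are open to someone who follows the text:

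- Apply Bonferroni to the two primary events. Healing is then judged at 2.5%, a level the sample size did not use.
- Keep 5% for each primary event. Either of two unordered results could then be presented as a positive primary finding.

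A healing p-value between 0.025 and 0.05 is positive on one course and negative on the other. In an open trial of 40 participants, that choice should not remain available once the data are in.

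**Working it through.** **Inputs.** Healing 75% and 30%, 20 per arm, two-sided 5%, power 80% (*Sample size*). Two distinct primary events (*Primary outcomes*). Pearson or Fisher (*Sample size and Statistics*). Assumption: if Bonferroni applies to the primary outcomes, the family has two members, because limb salvage and absence of major amputation are the same event. The per-test level is then 0.05/2 = 0.025.

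**1. Reproduce the plan's own figure.** Pooled-variance formula, with mean proportion (0.75 + 0.30)/2 = 0.525:

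n = [z(1−α/2)·√(2·0.525·0.475) + z(0.80)·√(0.75·0.25 + 0.30·0.70)]² / 0.45²

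At α = 0.05: [1.960·0.7062 + 0.8416·0.6305]² / 0.2025 = 1.915² / 0.2025 = 18.1, so 19 per arm. The planned 20 is consistent with this. The approximate power at 20 is Φ[(0.45·√20 − 1.960·0.7062)/0.6305] = Φ(0.997) = 84.1%. The printed sample size is therefore sound for a single unadjusted test.

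**2. The same calculation at 2.5%.** [2.241·0.7062 + 0.8416·0.6305]² / 0.2025 = 22.1, so 23 per arm. The approximate power at 20 is Φ(0.681) = 75.2%.

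**3. Exact power at 20 per arm.** Sum the product of the two binomial probabilities over all 21 × 21 outcomes in which the test's p-value is below α:

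| Test | α = 0.05 | α = 0.025 |
|---|---|---|
| Pearson, uncorrected | 82.3% | 73.1% |
| Fisher | 73.1% | 67.7% |

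The figure 73.1% appears twice because, at 20 per arm, Pearson at 0.025 and Fisher at 0.05 reject exactly the same tables. For 80% exact power at 0.025, Pearson needs 23 per arm (82.9%; 22 gives 79.5%) and Fisher needs 25 (81.0%).

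The unpooled normal approximation is kinder: 89.1% at 0.05 and 82.9% at 0.025. Exact enumeration of the tests that the plan names does not support those values.

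**4. Error rate if both primary events are tested at 5%.** For two independent tests of exact size 5%, the familywise error is 1 − 0.95² = 9.75%. Exact sizes at 20 per arm differ from 5%. The document gives no amputation rate, so null rates have to be assumed:

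| Null healing | Null amputation | Pearson | Fisher |
|---|---|---|---|
| 30% | 5% | 6.4% | 2.7% |
| 30% | 10% | 9.0% | 3.6% |
| 30% | 30% | 10.4% | 4.9% |
| 50% | 5% | 5.4% | 2.2% |
| 50% | 30% | 9.4% | 4.5% |

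Each entry is 1 − (1 − size for healing)(1 − size for amputation). For example, Pearson with both rates at 30% gives 1 − (1 − 0.0533)² = 10.4%.

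**The case against.** **A Bonferroni correction and a 5% level can coexist.** The 5% may be the level after adjustment, or Bonferroni may be meant only for the many secondary and repeated comparisons. A reader might infer that the two sentences flatly contradict each other; the text does not establish that. But neither reading removes the problem. If 5% is the adjusted level across the primary events, healing is tested at 2.5% and the power falls. If Bonferroni is only for secondary outcomes, the two primary events stand at 5% each with no order.

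**An unnamed family is detail for an analysis plan.** That is fair for the omission alone. What the article does fix is a sample size for one unadjusted test and a primary list with two events, and these do not match as written.

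**There may be only one primary efficacy outcome.** The abstract says "The main efficacy outcome will be partial or complete healing of the wound", and the sample size also rests on healing. The efficacy line could also mean that epithelialization and limb salvage must both succeed. In that case alpha needs no split, but the power for both is at most that for healing and has not been calculated. This is the best counter-reading, and the document does not state it.

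**Three outcomes could be counted.** A reader might divide alpha by three. That counts amputation twice, so two is the defensible number.

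**The error rate need not exceed 5%.** This stands for Fisher: at the null rates checked it is 2.2% to 4.9%. Inflation above 5% can be claimed only for Pearson. Fisher's protection has a price, since healing power is 73.1% at an unadjusted 5%. Part of any power shortfall therefore comes from the choice of test and not from Bonferroni.

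**Conclusion.** The point holds in a limited form. The 20 per arm is not an arithmetic error; it reproduces for one unadjusted 5% test. What the article does not secure is 80% power and 5% familywise control together for the primary list it gives.

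- With Bonferroni over the two primary events, healing power is about 73% (Pearson) or 68% (Fisher).
- Without it, Pearson gives a familywise error of 5.4% to 10.4% at the null rates checked. Fisher keeps it below 5% but has 73% power for healing.

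These figures rest on a family of two, independence of the two tests, the planning rates of 75% and 30%, and assumed null rates, because the document gives no amputation rate. Correlation between the events or rare amputations would lower the error figures. The documents do not support reading the two sentences as irreconcilable, counting three primary outcomes, or saying that the error rate exceeds 5% whichever test is used. The text should be changed because the primary threshold remains open and closing it is cheap.

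**What to change.** In *Sample size and Statistics*:

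1. Name total epithelialization per participant as the primary efficacy test, at two-sided 5%.
2. Test limb salvage, counted once, at 5% only if healing is significant. Otherwise report it with a confidence interval.
3. Confine Bonferroni to a named set of secondary comparisons.
4. Name one test, Pearson or Fisher, for the primary comparison.

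In *Sample size*, restate the power for that test and level: 82% (Pearson) or 73% (Fisher) at 5%. If Bonferroni over the two primary outcomes is preferred, the figures are 73% or 68% at 2.5%.

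A fixed sequence is not the only valid design. It is proposed because it keeps the alpha used for sizing and controls the familywise error at 5%. The change is to wording and needs no extra participants or data. It does have a price: limb salvage cannot be claimed confirmatorily if healing is not significant, and the stated power may fall below 80%, depending on the test chosen.

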### Strengths and limitations

The strong point of the study is that it is a RCT for a disease stage that has practically no solution. Through the methodology employed, it will be possible to conclude the safety and efficacy of cell therapy for PAD plus critical ischemia and ulcers.

Limitations to this study include the impossibility of performing biopsies and tracking the applied stem cells.

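### Safety outcomes go through the same 5% difference tests as efficacy, with an open-ended Bonferroni step, yet the protocol says the method lets safety be concluded; a non-significant result in 20 v 20 cannot show that

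*Protocol article*

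**What the plan says.** The Sample size and Statistics section of the protocol article puts all monitored data under one rule: "All data monitored in the study for Group 1 (cell therapy) and Group 2 (control) will be statistically compared". The level is also common to all: "In all statistical tests, the significance level of the independent variable will be set at 5% (p < 0.05". Between these two sentences stands the multiplicity step, with no family of tests named: "Bonferroni coefficient and multivariate analysis will also be used".

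For categorical data the section first offers Pearson's chi-square or Fisher's exact test. Its last paragraph names Fisher's exact test with no alternative. The section also plans descriptive statistics with contingency tables, Cox regression and Kaplan-Meier curves.

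Safety is a primary outcome (absence of major amputation, under Primary outcomes). Secondary outcomes adds a long list of events and laboratory changes. No separate rule for comparing safety is given. The Adverse effects section also relies on significance: the interim look halts the study if a safety outcome differs significantly.

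Strengths and limitations draws the inference: "Through the methodology employed, it will be possible to conclude the safety and efficacy of cell therapy".

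The sample size rests on healing alone: "estimated proportion of the ulcer healing rate of 75% for group 1" against "30% for group 2, which will be treated with hydrogel dressing".

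**The concern.** Efficacy and safety ask different things of a test. For efficacy, a significant difference is the evidence sought, and a multiplicity correction guards against a false claim of benefit. For safety, the reassuring result is the absence of a difference, and a difference test cannot supply that. A p-value above 0.05 may mean no excess of harm, or too few participants to see one. With 20 per arm and uncommon events, the second explanation is usually available. A Bonferroni step applied to harms lowers sensitivity further, in the direction that favours the new treatment.

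The analysis rule and the conclusion announced under Strengths and limitations therefore do not fit together. In a phase I/II trial the safety statement is likely to be carried into the next study. If it rests on non-significance, it may accompany data that are compatible with a large excess of harm.

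**Working it through.** **Inputs from the protocol article.** 20 per arm, 1:1 ("the sample was defined as 20 participants for group 1 and 20 participants for group 2 (1:1 allocation"); two-sided 5% and 80% power ("Assuming a test power of 80% and a significance level of 5% for a two-sided test"); healing 75% v 30%. **Assumptions, not in the document:** the event counts, the true event rates, and the number of tests m in a Bonferroni family.

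**1. The plan's own figure.** For two proportions with pooled variance,

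n = [1.96·√(2·p̄·(1−p̄)) + 0.842·√(p1(1−p1) + p2(1−p2))]² / (p1−p2)², with p̄ = (0.75 + 0.30)/2 = 0.525.

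This is [1.96·√0.49875 + 0.842·√0.3975]² / 0.45² = (1.384 + 0.531)² / 0.2025 ≈ 18.1, so 19 per arm. The stated 20 is reproduced. It is sized for a 45-point difference in healing and not for any safety outcome.

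**2. Two-sided Fisher p-values, 20 v 20.** With margins fixed, the probability of 4 v 0 is C(20,4)/C(40,4) = 4,845/91,390 = 0.0530. The mirror table is equally likely, so p = 0.106. For 6 v 1 the upper tail is [C(20,6)·C(20,1) + C(20,7)]/C(40,7) = (775,200 + 77,520)/18,643,560 = 0.0457, so p = 0.091.

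| Control events | Largest non-significant Group 1 count | Smallest significant Group 1 count |
|---|---|---|
| 0 | 4 (p = 0.106) | 5 (p = 0.047) |
| 1 | 6 (p = 0.091) | 7 (p = 0.044) |
| 2 | 8 (p = 0.065) | 9 (p = 0.031) |

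**3. Pearson chi-square on the same tables.** Uncorrected, 4 v 0 gives χ² = 40·(4·20 − 16·0)²/(20·20·4·36) = 4.44, p = 0.035. For 6 v 1, χ² = 40·(6·19 − 14·1)²/(20·20·7·33) = 4.33, p = 0.037. With Yates' correction the p-values are 0.114 and 0.096. The expected event counts are 2 and 3.5 per arm, where Fisher is the usual choice.

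**4. Bonferroni, if it covers safety.** The threshold is 0.05/m. At m = 2 it is 0.025, and neither table is significant by Fisher, Yates or uncorrected Pearson. Fisher would then need 6 v 0 or 8 v 1. At m = 10 (threshold 0.005) it would need 8 v 0 or 10 v 1.

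**5. Exact Fisher power.** This is the sum of Bin(a; 20, p1)·Bin(b; 20, p2) over all tables (a, b) with p below the threshold.

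| Assumed true rates | 5% level | 0.5% level (m = 10) |
|---|---|---|
| 20% v 5% | 17% | 1% |
| 30% v 10% | 24% | 4% |
| 30% v 5% | 45% | 10% |

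Uncorrected Pearson at 5% gives 29%, 36% and 59% for the same three rows.

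**6. What an interval would show.** The Newcombe 95% interval for the risk difference is −0.1 to +41.6 percentage points for 4/20 v 0/20 (estimate +20), and +0.8 to +47.3 points for 6/20 v 1/20 (estimate +25). Either makes plain that a large excess has not been excluded.

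**The case against.** Much can fairly be said for the plan.

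- A reader might infer that safety is judged by these tests alone. It is not. Contingency tables are planned, so 4/20 v 0/20 would be visible, and the Kaplan-Meier and Cox analyses could apply to amputation and death. Laboratory values treated as quantitative would go to other tests, so the Fisher examples do not apply to them.
- A reader might infer that 4 v 0 and 6 v 1 would certainly be reported as non-significant. That depends on the test. Uncorrected Pearson is named once in the section and finds both significant at 5%.
- A reader might infer a Bonferroni correction across every safety item. Counting about 36 outcomes would give a threshold of 0.05/36 = 0.0014, which even 8 v 0 (p = 0.0033) would miss. The document defines no such family and does not say that Bonferroni covers safety.
- A reader might infer that p ≥ 0.05 will be declared safe. The article nowhere says so. In the Adverse effects section, significance serves to detect harm.
- Confidence intervals are often left to the analysis plan, which is not shown, and this article is condensed. Their absence is no defect by itself. Low power for harms comes with any 20-per-arm trial, and an interval adds no data: the one for 4 v 0 also just includes zero.

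All of this stands, and it limits the point. It does not remove the mismatch between the rule that is stated and the conclusion that is stated. The universal 5% rule and the unrestricted Bonferroni sentence are in the text, and an analysis plan that follows them inherits them. The claim that safety can be concluded is also in the text, and more favourable test choices do not make a non-significant difference into evidence of safety.

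**Conclusion.** The point holds in a limited form. The article applies one 5% difference-test rule to all monitored data, does not exempt safety from Bonferroni, and says the methodology allows safety to be concluded. Non-significance in 20 v 20 cannot carry that conclusion. By Fisher's exact test, an excess of 4 v 0 or 6 v 1 passes unflagged, and a true fourfold (20% v 5%) or threefold (30% v 10%) event rate would be detected 17% or 24% of the time.

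These sizes rest on assumed counts and rates and on Fisher as the operative test, which the section's last paragraph supports. Under uncorrected Pearson both example tables are significant at 5%, but not once Bonferroni spans two or more tests. Whether it would do so for safety is open. The documents do not support the stronger reading that harms will be concealed or that a non-significant p-value will formally be called safe.

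**What to change.** In Sample size and Statistics, add a rule for safety: binary safety outcomes are reported per arm as number and percentage, with the risk difference and its 95% Newcombe confidence interval; no multiplicity correction is applied to safety outcomes; and p ≥ 0.05 is not taken as evidence of safety. This also settles whether Bonferroni reaches safety.

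In Strengths and limitations, replace the claim that safety can be concluded with a statement that the trial estimates safety with limited precision.

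The cost is some wording and one extra column in the safety tables. Sample size and procedures do not change. The downsides are a less favourable safety statement and, without correction across many outcomes, more safety signals that arise by chance and must be read as such.
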